The following are the aims of the present pilot study: (1) to determine whether a full trial is justified, (2) to establish the effect size on the primary outcome (voice-related distress) for a sample size calculation for a definitive trial, and (3) to address questions concerning study recruitment, retention, and acceptability. Specifically, between-group treatment effects will determine whether a definitive RCT of guided self-help CBTv is justified; that is, we will proceed if the effect size on the primary outcome is in favor of CBTv in comparison to the delayed therapy control condition and if the 95 % CI for this effect contains the minimal clinically important difference (MCID). If so, this study will provide the parameters needed to estimate the sample size for a definitive RCT. Finally, we will assess whether the study design is acceptable to participants using recruitment and retention rates and qualitative interviews with participants. Both study dropout and therapy dropout rates will be reported with a view to understanding reasons for dropout and developing strategies to minimize dropout in a definitive trial.

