### Participants

Participants will be service users recruited from an NHS mental health trust in the South of England. Clinicians will be asked to refer eligible service users from among their caseload. Potential participants will also be identified using a database of people who have agreed to be contacted about research studies.

In line with the recommendations of Julious [27] for pilot RCTs, 12 participants per arm are required for this pilot RCT. The authors of a meta-analysis of briefer forms of CBTp found the maximum dropout rate to be 13.5 % [21]. Using this as a guideline, we have overestimated a potential attrition rate of 20 % for the present study, meaning a total of 30 participants will be recruited (15 per arm).

The inclusion criteria for participants are that they must (1) be aged 18 years or older; (2) be distressed by hearing voices; which will be operationalized by requiring participants to score at least 3 out of 5 on item 5 (How much do the voices interfere with your daily activities?), 6 (How distressing are the voices that you hear?), or 7 (How bad do the voices make you feel about yourself) on the Hamilton Program for Schizophrenic Voices Questionnaire (HPSVQ) [28], equivalent to moderate levels of interference, distress, and impact, respectively; (3) have heard voices for the at least 1 year; (4) are not currently in, or have plans to receive, another psychological intervention during the course of the study; and (5) are able to read and write in English at the level required for the self-help course.

Participants will be excluded from the trial if they have a primary diagnosis of substance misuse or if an organic illness is determined as the reason for hearing voices. Otherwise, diagnosis is not an inclusion or exclusion criterion, given that distressing voices are common across a range of diagnoses (i.e., schizophrenia [3], borderline personality disorder [4], dissociative identity disorder [5], bipolar disorder [6], posttraumatic stress disorder [7]).

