### Planned analysis

All of the analyses will be carried out once data collection has been completed. IBM SPSS Statistics version 22 software (IBM, Armonk, NY, USA) will be used to conduct all quantitative analyses. The findings of this trial will be reported using the Consolidated Standards of Reporting Trials (CONSORT) guidelines. The recruitment rates for this trial will be reported as a ratio of the number of potential participants approached to the number who consent to participate. The retention rates will be reported first as the percentage of participants who drop out of the study (i.e., do not complete time 1 assessments) and second as the percentage of participants who drop out of therapy before exposure (receive fewer than four sessions). If study or therapy dropout rates are greater than 33 %, this will indicate that changes to the study and/or therapy protocols may be needed. The acceptability of the study and therapy will be assessed using retention rates and feedback obtained through the exit interview.

The analysis for this trial will be mostly descriptive. We will report the means and/or medians (as appropriate) as well as SD and minimum and maximum scores at time 0 and time 1 for both groups on primary and secondary outcomes. Participants’ characteristics will be reported using frequency counts and percentages, including the characteristics of any participants who drop out of the study and/or therapy. Analysis of covariance will be used to estimate T1 between-group differences on primary and secondary measures, controlling for baseline scores. Ninety-five percent confidence intervals will be calculated. Effect sizes will be reported as Cohen’s *d* (unstandardized effect size divided by the baseline pooled SD). We will look at the effect sizes using both an intention-to-treat analysis approach and a per-protocol analysis (looking only at participants who attended at least 50 % of therapy sessions). A definitive trial will be considered to be justified if there is a between-group effect in favor of CBTv on the primary outcome (HPSVQ voice impact subscale [28]) and if the 95 % CI contains the MCID of 2 points in favor of CBTv.

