The exit interviews will be transcribed into NVivo software files (QSR International, Doncaster, Australia) and analyzed using thematic analysis in accordance with the Braun and Clarke [41] protocol. The aim of the analysis will be to identify common patterns across interviews that reflect the participants’ experiences of therapy and of the study processes. These themes, as well as the quantitative results, will be used to refine the study and therapy protocols. If a definitive trial is justified, then the power calculations will be based upon the between-groups effect size on the HPSVQ voice impact subscale [28].

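### The definitive trial is to be sized on the effect observed in about 24 pilot participants, which is too imprecise for that use; the 2-point MCID already in the plan should set the target difference

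*Protocol article*

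**What the plan says.** All references are to the Protocol article.

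- **Background (aims).** The second aim is "to establish the effect size on the primary outcome (voice-related distress) for a sample size calculation for a definitive trial".
- **Planned analysis, last paragraph.** If a definitive trial is justified, "the power calculations will be based upon the between-groups effect size on the HPSVQ voice impact subscale". The Discussion adds that the pilot's parameters will feed the later trial's design and sample size.
- **Planned analysis, progression rule.** A definitive trial is justified "if there is a between-group effect in favor of CBTv on the primary outcome" and if the 95% "CI contains the MCID of 2 points in favor of CBTv". Background gives the same two conditions without the figure. The MCID is used only here.
- **Planned analysis, estimator.** The between-group difference at 12 weeks comes from ANCOVA adjusted for baseline. Cohen's d is that difference divided by the pooled baseline SD.
- **Participants.** "12 participants per arm are required for this pilot RCT", following a published recommendation for pilot trials, and recruitment is raised to 30 to allow for 20% attrition.

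No shrinkage, confidence limit or lower bound is attached to the effect size used for sizing.

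**The concern.** Required sample size varies with the inverse square of the assumed effect, so halving d quadruples the trial and doubling d cuts it to a quarter. A d from about 24 people is uncertain over a wider span than that. A pilot that happens to overshoot yields a definitive trial too small to detect the difference the authors regard as clinically important. One that undershoots yields a trial nobody could run. The sample size for the definitive trial is one of the pilot's three stated aims, so the rule for deriving it matters.

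**Working it through.** **Inputs from the document.** 12 evaluable per arm, 15 per arm recruited, 1:1 allocation, ANCOVA on baseline, 95% CI, d scaled by the baseline SD, MCID 2 points on a subscale of five items scored 0–4 (range 0–20).

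**Inputs assumed because the document gives none.** SD 4 points (range 3–5), baseline to follow-up correlation r = 0.5 (range 0.5–0.7), equal SDs at both times, normal outcomes, definitive trial at two-sided 5% and 90% power, true effect 0 to 3 points.

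**1. The plan's own figure.** 12 / (1 − 0.20) = 15 per arm, 30 in total. This reproduces. The 12 is a pilot rule of thumb, so there is no power figure to check.

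**2. Precision of d.** Half-width ≈ t × √(2(1 − r²)/n).
- 12 per arm: 2.08 × √(2 × 0.75/12) = 0.74. Simulation, which also allows for the estimated SD and chance baseline imbalance, gives a median of 0.75.
- 15 per arm: 2.05 × √(2 × 0.75/15) = 0.65, simulated 0.66.

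**3. What this does to n.** n per arm = 2 × ((1.96 + 1.2816)/d)² ≈ 21.0/d². All three values of d below lie within ±0.75 of a true 0.5:

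| d used | n per arm |
|---|---|
| 0.25 | 337 |
| 0.50 | 85 |
| 1.00 | 22 |

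**4. Size actually needed for 2 points at SD 4.** Unadjusted: 2 × 16 × 3.2416²/4 = 84.06, so 85 per arm. With ANCOVA: 84.06 × (1 − 0.25) = 63.04, so 64 per arm.

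**5. Simulation of the rule as written** (12 per arm, SD 4, r = 0.5, true effect 2 points). Each pilot that passes has its d converted to n as in step 3.
- 10th to 90th centile of n: 22 to about 840 per arm. The upper centile varies between about 800 and 840 from run to run.
- Definitive trial analysed by ANCOVA: true power below 80% in about 34% of cases and below 50% in about 11%.
- Definitive trial analysed unadjusted: about 45% and 20%.
- With 15 per arm: 25 to about 720 per arm, and about 32% and 8% under ANCOVA.
- Over SD 3–5 and r 0.5–0.7 at 12 per arm, the ANCOVA figure for power below 80% runs from about 10% (SD 3, r = 0.7) to about 40% (SD 5, r = 0.5).

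**6. Hand check of the 34%.** With ANCOVA, 80% power needs 48 per arm (62.8 × 0.75 = 47.1, rounded up). By step 3, n falls below 48 when the pilot d exceeds √(21.0/48) = 0.66, only 0.16 above the truth. The standard error of d is about 0.75/2.08 = 0.36, so this happens with probability 1 − Φ(0.16/0.36) ≈ 0.33. Removing the 2.5% of pilots whose CI lies wholly above 2 points, and dividing by the pass probability of about Φ(0.5/0.36) − 0.025 ≈ 0.89, gives about 0.34.

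**7. Contribution of the progression rule** (12 per arm, SD 4, r = 0.5):

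| True effect (points) | Mean estimate among pilots that pass |
|---|---|
| 0 | 1.15 |
| 1 | 1.6 |
| 2 | 2.2 |
| 3 | 2.8 |

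The upward shift is material at 0 and 1 point and small at 2. It reverses at 3, where about 10% of pilots are stopped because their whole CI lies above 2 points.

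**The case against.** Four points can be made for the plan.

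- **The wording is loose.** The effect size forms the basis of the calculation and the parameters inform it, so a cautious author could still use a confidence limit or a lower bound. That is possible, but the observed effect is the natural reading of the second aim and no safeguard is stated.
- **The analysis is described as mostly descriptive.** The means, SDs and dropout needed to size on 2 points will be collected anyway. This is correct and makes the fix cheap, but it does not undo the commitment to use the observed effect.
- **The harm falls on a later trial,** which will need its own justification and can correct the matter then. This stands, and it limits the severity.
- **The MCID is given without a derivation.** This also stands. It is a defensible target, and it is the difference the authors themselves chose for the decision to proceed, but the document does not show that it is the only right one.

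A reader might also infer that the progression rule lets through only inflated estimates, so that selection drives the undersizing. The document does not support that. The second condition requires the CI to contain 2 points, so the rule rejects the largest estimates as well as unfavourable ones. When the true effect equals the MCID, the spread in n comes almost entirely from small numbers.

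**Conclusion.** The concern holds as one of imprecision. An effect size with a 95% CI of about ±0.75 (±0.66 with full retention) cannot be established well enough to size a trial. When the truth is exactly the MCID, the stated rule gives a roughly one in three chance of a definitive trial with less than 80% power under ANCOVA, at SD 4 and r = 0.5. That chance varies from about 10% to 40% over the SDs and correlations considered. The higher figures of 45% and 20% apply only if the definitive trial drops baseline adjustment, which would depart from this pilot's own method. The SD, correlation, target power and true effect are assumptions, so the percentages are illustrative. The instability does not depend on any single value.

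A reader might take this to mean that the pilot itself is unsound. It does not: randomization, data collection, estimates and CIs are unaffected. The point should be fixed, but it does not block the pilot.

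**What to change.** Change two sentences. In the last paragraph of Planned analysis, state that the definitive trial will be sized to detect the 2-point MCID on the HPSVQ voice impact subscale. In Background, reword the second aim so that the pilot estimates the quantities needed for that calculation: the follow-up SD, the baseline to follow-up correlation (together giving the ANCOVA residual SD) and dropout. Report the pilot effect and its 95% CI as descriptive.

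Preferably use an upper confidence limit for the SD, because that too is estimated from few people. With 24 participants and 21 degrees of freedom, the one-sided 80% limit is √(21/15.44) = 1.17 times the estimate.

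Sizing on 2 points at 90% power gives 48, 85 or 132 per arm for SD 3, 4 or 5 unadjusted, and 36, 64 or 99 with ANCOVA at r = 0.5, before dropout. At SD 4 with ANCOVA, the upper limit raises 63.04 to 63.04 × 1.36 = 85.7, so 86 per arm.

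The cost is wording only, with no new data or visits. The drawback is that the planned definitive trial may be larger than one based on a favourable pilot estimate.

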### Research governance

This protocol has been prepared in line with the Standard Protocol Items: Recommendations for Interventional Trials (SPIRIT) guidelines [42, 43]. See Fig. 2  and additional material for a copy of the SPIRIT figure and checklist for this study.

**Fig. 2 Fig2:**
[figure not shown]
Schedule of enrollment, intervention, and assessments. *CBTv* cognitive behavioral therapy for voices

The trial is sponsored by the University of Sussex and funded through a doctoral studentship award given to CMH by the Economic Social and Research Council (ES/J500173/1) and Sussex Partnership NHS Foundation Trust. Ethics approval has been granted by the NHS Health Research Authority North West – Lancaster Research Ethics Committee (REC) (15/NW/0575). Written informed consent will be obtained from each participant by the lead author. A copy of the participant information sheet and consent form can be obtained from the corresponding author.

A Trial Steering Committee (TSC) will be established in accordance with Medical Research Council guidelines [44] and will monitor the conduct of the trial and adherence to the study protocol. The TSC will include an independent chair, independent experts, and lay members. If necessary, applications to make significant protocol amendments will be made to the REC and study sponsor. A Data Monitoring Committee is not deemed necessary, given the pilot nature of the current study.

The U.K. National Institute of Health Research Good Clinical Practice guidelines will be followed, which includes reporting and investigation of any adverse events during the study. In line with these guidelines, the research team will ensure that the patient care team members are aware of any adverse events. If an adverse event is deemed to be related to the study, it will be reported to the study sponsor. The sponsor will then determine whether the study needs to be stopped and if an investigation of the adverse event is needed.

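### The only stated route to a decision on stopping the study runs through a case-by-case relatedness judgement, which does not fit the promise to report and investigate any adverse event

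*Protocol article*

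**What the plan says.** All the relevant text is in the Research governance section of the protocol article.

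- **General commitment.** Good Clinical Practice guidelines will be followed, "which includes reporting and investigation of any adverse events during the study". No relatedness condition is attached.
- **Care team.** Under the same guidelines, "the research team will ensure that the patient care team members are aware of any adverse events". Again there is no relatedness condition.
- **Sponsor.** "If an adverse event is deemed to be related to the study, it will be reported to the study sponsor". The verb is passive and the assessor is not named.
- **Decision.** "The sponsor will then determine whether the study needs to be stopped and if an investigation of the adverse event is needed".
- **Data Monitoring Committee.** "A Data Monitoring Committee is not deemed necessary, given the pilot nature of the current study".
- **Trial Steering Committee.** It "will monitor the conduct of the trial and adherence to the study protocol". On membership: "The TSC will include an independent chair, independent experts, and lay members". Neither adverse event review nor advice on stopping is named as part of its task.

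**The concern.** The general commitment covers any adverse event, for reporting and for investigation alike. The operating rule that follows makes reporting to the sponsor conditional on a judgement of relatedness, and the decision whether to investigate comes only after that report. Read literally, an event judged unrelated is both promised an investigation and left outside the only process described for deciding on one.

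The statistical point is that a relatedness filter works on single events, whereas a randomized trial offers a comparison of arms. Everyone enrolled already hears distressing voices, so deterioration can occur with or without the therapy, and one event in one person is hard to attribute. An excess in one arm can consist entirely of events that each look unrelated. If those events stop at the filter, the body that decides whether the study continues lacks the numerators from both arms.

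At stake is oversight while the trial is running. A harms table published at the end would inform a definitive trial but could not inform a decision to stop this one.

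**Working it through.** The article states no figure for adverse events, so the main check is a reading of the text. The arithmetic only shows what a listing by arm could and could not deliver.

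**1. Who learns of which events, as written**

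| Recipient | Events covered | Stated power |
|---|---|---|
| Research team | Any (it informs the care team) | None stated on stopping |
| Patient care team | Any | None stated on stopping |
| Sponsor | Those deemed related to the study | Decides on investigation and on stopping |
| Trial Steering Committee | Not stated | Conduct and protocol adherence |
| Data Monitoring Committee | Does not exist | None |

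The parties stated to know of all events have no stated role in stopping. The party that decides is stated to receive only a filtered set. A care team sees its own patients and not the two arms. The sentence on the sponsor's decision uses the word *then*, which ties that decision to the report in the sentence before it.

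**2. Consistency of the paragraph**

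Reporting and investigation of any event (general commitment) stands against reporting to the sponsor, and a decision whether to investigate, for related events only (operating rule). Both could be true if some other body reports on and investigates unrelated events, but the article names none.

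**3. Numbers per arm**

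Inputs from the Participants section: 12 per arm required, 20% attrition.

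12 / (1 − 0.20) = 15 per arm, and 2 × 15 = 30 in total. This reproduces the plan's figure.

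**4. Illustration with assumed event rates**

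The documents give no rates. Assume that 20% of delayed-therapy and 40% of immediate-therapy participants have an event:

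- 0.20 × 15 = 3 and 0.40 × 15 = 6 participants.
- If each event is judged unrelated, the number that the stated rule sends to the sponsor is 0.

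The last line follows from the rule and the assumption together. It shows what the rule permits and does not estimate how often that would happen.

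**5. What a comparison could show**

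- Fisher's exact test for 3/15 against 6/15, with 9 events in 30 people: two-sided p = 2 × [C(15,0)C(15,9) + C(15,1)C(15,8) + C(15,2)C(15,7) + C(15,3)C(15,6)] / C(30,9) = 2 × 3,054,480 / 14,307,150 = 0.43.
- Power of Fisher's test at true rates of 20% and 40%, 15 per arm: about 11%.
- Normal-approximation power at two-sided 0.05, 15 per arm: 27% for 10% against 30%, 47% for 10% against 40%, 40% for 20% against 50%. For the first of these: pooled rate 0.20; null standard error √(0.20 × 0.80 × 2/15) = 0.146; alternative standard error √((0.09 + 0.21)/15) = 0.141; Φ((0.20 − 1.96 × 0.146)/0.141) = 0.27.

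A listing by arm would therefore support clinical and steering judgement. It would not serve as a test.

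**The case against.** The case on the other side is substantial, and much of it stands.

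- **A reader might infer that unrelated events are never seen.** The text contradicts this. The research team must know of any event in order to inform the care team, and the general commitment covers any event. The filter restricts one recipient, the sponsor.
- **A reader might infer that events will never be compared between arms.** The article neither plans nor excludes a listing by arm. It commits to CONSORT reporting, and a harms table is commonly left to a fuller document. Its absence here is not a finding.
- **A reader might infer that the research team makes the judgement and that the sponsor decides alone.** The assessor is unnamed. The sponsor is the only decision-maker named, but nothing prevents an independent steering committee from raising a safety concern.
- **A reader might infer that delayed-therapy events cannot count as related.** The criterion is relatedness to the study and not to the therapy. That group also goes through consent, randomization, assessments and a wait of about 12 weeks, so an event there can qualify.
- **A reader might infer that the trial has no safety comparison at all.** Voice-related distress is the primary outcome. It is compared between arms by ANCOVA with a 95% confidence interval, and a definitive trial requires an effect in favor of CBTv. An estimated average worsening under therapy would be visible and would block progression.
- **The illustration rests on assumed rates, and the trial is too small to detect most imbalances.** Both are true.

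These points narrow the concern but do not remove it. The relatedness condition is a stated rule and not a silence. The primary outcome is measured at T1, with all analysis after data collection is complete, and it does not capture discrete serious events. Neither it nor a final CONSORT table gives the decision-maker information during the trial.

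**Conclusion.** The concern holds in a limited form. The Research governance section makes a commitment covering any adverse event and then a reporting rule covering only related ones, and the only stopping and investigation decision it describes depends on the narrower rule. With no Data Monitoring Committee and no stated safety review by the Trial Steering Committee, serious events judged unrelated one at a time need not reach the body that decides on stopping, even if they accumulate in one arm.

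The conclusion rests on the wording of the article alone. It assumes that no fuller document gives the sponsor or the steering committee a separate, unfiltered route. If one does, the article's sentence should be brought into line with it. No numerical size can be attached: the 3 against 6 of 15 is an assumed example, and nothing in the documents says how often such events would occur or be judged unrelated. The point merits correction because it concerns safety oversight and is cheap to repair. It does not show that harms would be concealed or that the trial's results would be biased.

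**What to change.** Reconcile the two statements by changing the reporting sentence:

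1. All serious adverse events, in either arm, go to the sponsor and to the existing Trial Steering Committee, whatever their judged relatedness. The article does not use the category serious, so the text should point to the definition that applies.
2. Relatedness is recorded as a data item, with the role of the assessor named. It no longer decides who is told.
3. Events are listed descriptively by allocated arm from randomization to T1, giving the number of participants with at least one event and the number of events, with no significance test.

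The listing supports the changed rule. Its absence from the article would not be a point by itself. No new committee is needed, because the steering committee already has an independent chair and independent experts. A listing by arm should not pass through the rater who conducts the blinded T1 assessments.

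The cost is one reworded sentence, one short descriptive listing, and a few additional reports to the sponsor and steering committee in a trial of 30 people.
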